##### Assessment Training and Exercise Supervision Training

Site leads or other trained staff will provide training in the processes required for the in-person measurements, completing the fidelity checklists, and supervising the exercise sessions.

##### Competency Assessment

Coaches are required to undertake a competency assessment prior to delivery of the SSBC Australia program. The protocol and standards for coach competency assessment were designed and tested by SSBC Canada. In line with the Canadian model, assessment of competency includes 4 elements: knowledge of the program content, ability to conduct the in-person measurement protocol, ability to appropriately supervise the exercise sessions (or provide guidance on appropriate exercise sessions to attend if a site chooses to use group-based exercise), and ability to use appropriate MI skills. Knowledge will be assessed via a 20-item survey, which has been adapted from the Canadian knowledge check to align with the Australian-specific content. A pass mark of at least 70% (14/20) is required to achieve competency, with coaches able to repeat the survey as required until they meet this pass mark. Scores and the number of passes on the first attempt will be recorded. The site-level trainer or the research team will assess competency in the in-person measurement and exercise supervision protocol. For assessment of competency in MI, coaches will undertake a mock session of the first health coaching session, with assessment conducted by the research team using the Abbreviated Motivational Interviewing Competency Assessment tool [49] and a checklist against delivery of session content. In line with the Canadian SSBC coach training [11,22], the coach will be provided with feedback on their mock session by the research team (who have been trained in the use of the Abbreviated Motivational Interviewing Competency Assessment tool), with a minimum score of 0.5 of 2.0 for each of the 5 criteria required to meet competency. Potential coaches can repeat any component or part thereof to meet competence.

##### SSBC Australia REDCap Coach Training Database

An Australian-specific implementation strategy was the development of a REDCap database to allow staff to easily guide and track the coach training process and evaluate the training. The database also enabled the collection of data from coaches regarding their perspectives on the SSBC Australia program at various intervals after completing the training. For student coaches, data were collected at the end of their placement and at 1 month and 1 year later; for all other coaches, data were collected at 2 months, 1 year, 2 years, 3 years, and 4 years after the training. Research staff and site staff performing the training use this database to add records for new trainee coaches, send out the required training steps in order, receive alerts indicating when each step is done, fill in competency checklists for the mock session assessments (MI, measurement, and exercise supervision), and send iterative and final feedback to the trainees, as well as to notify relevant staff when competent coaches will require access to the REDCap client database. The steps trainees perform are completing consent forms, completing pretraining surveys, following instructions to join the Online 3C Training platform (and undertake that training), successfully complete a knowledge check or a supplemental knowledge check (if the first check is failed), and use links they are sent of the practice coaching forms for the mock session assessments. After they have completed their mock session assessments, they complete posttraining surveys, receive final feedback on their mock assessments, and complete ongoing surveys tracking training outcomes and their perspectives on the training at various time points after the training.

#### Delivery of Program by Site (Delivery Funded by Research)

For the first 2 years, the delivery of the SSBC Australia intervention to clients will be primarily funded by the research grant, with in-kind support given by the delivery provider in relation to free gymnasium membership for the duration of the 6-session delivery (4 to 6 weeks).

Aligned with the Canadian model, the SSBC Australia intervention involves 2 key elements: the 6 individual coaching and exercise sessions with the trained SSBC coach and the client workbook.

##### Individual Coaching Sessions

The 6 individual sessions are delivered using an MI approach across a 3- to 4-week period (noting additional time up to 6 weeks is allowable if required by the site or client). Each session involves a coaching component for approximately 30-40 minutes and an exercise component for 20-30 minutes. Sessions 1 and 6 also have an assessment component (see Clinical Indicators (Objective Physical Assessments) section). Each coaching session includes a check-in with the client, provision of information around a session topic, planning and goal setting, and wrap-up.

Session topics covered in SSBC Australia include an introduction to the SSBC Australia program; healthy eating and identifying hidden sugars; physical sensations of cardiovascular exercise and strength training; carbohydrates, glycemic index, and a healthy plate; identifying barriers and enablers to active living; and managing setbacks and planning for success. Key changes from the SSBC Canada program were the alignment of recommendations to the Australian Physical Activity [50] and Healthy Eating [51] guidelines. This included the addition of material on hidden sugars, strength training (in line with evidence of the benefits of strength training for diabetes prevention [52]), and the importance of considering the 24-hour day [53], including the identification and impact of high sedentary time [54]. Selected by the participant, each exercise session involves either moderate-intensity continuous training or high-intensity interval training, with the duration of the exercise component increasing across the 6 sessions from 12 to 20 minutes in the first session, up to 30 minutes in each of the last 2 sessions. Delivery sites can choose to substitute or augment this core program with tailored elements such as virtual delivery of the coaching and use of group-based exercise classes. Provision and take-up of any substitutions or augmentations will be tracked. Scripts embedded in REDCap will be used to guide SSBC Australia coaches through the key points to cover in each session, in conjunction with data collection to monitor implementation fidelity.

##### Client Workbook

Clients will be provided with an SSBC Australia workbook, which will be used to guide the session activities. In addition to the educational content and session-based activities, there is also space for clients to monitor and track their progress toward their goals and reflect on their progress if they choose. The SSBC workbook was adapted to be suitable for an Australian delivery context (eg, the use of Australian rather than Canadian guidelines and examples of Australian rather than Canadian foods).

#### Community of Practice

The SSBC Canada team developed 2 communities of practice: one for SSBC coaches and one for site leads implementing the program. The Australian coaches and site leads will be invited to these virtual communities of practice to enhance and encourage learnings across all implementation sites. Engagement with the Canadian community-of-practice site will be monitored through the Canadian website [55] and a Microsoft Teams site. In addition, an online sharing site (Microsoft Teams) will be established to facilitate an Australian-based community-of-practice among SSBC Australia coaches and site leads at participating Australian sites, with engagement and meeting minutes recorded and reviewed.

#### Delivery of Program by Site (Delivery Funded by Site)

After 2 years of primarily research-funded delivery, sites will have the opportunity to decide whether they want to continue to deliver the program (with sites fully funding the delivery) or to not continue delivery. The research grant will continue to fund the evaluation of the program until the end of 4 years of implementation regardless of whether sites choose to continue the program or not after 2 years. Site and organization leads have committed to this evaluation for 4 years. A sustainability adaptation workshop will be conducted with each site that decides to continue delivery at both the end of year 2 (end of research-funded delivery) and the end of year 4 (end of research evaluation). SSBC Australia will be considered affordable on the APEASE criteria if the site decides to continue delivery of the program after 2 years.

### SSBC Australia Participants: Delivery Providers

#### Overview

SSBC Australia will be delivered across 2 providers and 5 sites in South-East Queensland: The Y Queensland (4 sites) and Logan Healthy Living (1 site). These sites were identified (1) to align with the delivery partner in Canada (Y Queensland) and (2) to address an identified need for a diabetes prevention program, which can be delivered by non–health professionals (including students), from a community-based primary care partner (Logan Healthy Living). Identification and recruitment of sites occurred as part of the grant funding submission process.

#### The Y Queensland

The Y Queensland is a not-for-profit organization with services including childcare, fitness, camping, education, recreation, and community programs [56]. The organization is aligned with the YMCA’s in Canada, which are the delivery sites for the SSBC Canada program [16]. There are 9 Y sites across South-East Queensland. In partnership with The Y leadership team, 4 sites were chosen as delivery sites for SSBC Australia: 1 inner city, 1 outer city, and 2 regional. It was expected that these sites would provide an appropriate mix of participants and resource availability to be able to inform the sustainability and potential scale-up of the program.

#### Logan Healthy Living

Logan Healthy Living by UQ Health Care is a community-based allied health service designed to support adults living in the Logan area with, or at risk of, type 2 diabetes [34]. Logan is a culturally diverse and relatively low-income region in South-East Queensland. The region experiences rates of diabetes higher than the Queensland average (5.2% vs 4.5% [57]), with diabetes the most common cause of potentially preventable hospitalizations [58]. Logan Healthy Living was designed to address this need, with details of the clinic development and service provision reported previously [34]. In brief, this multisectorial health hub model, which was established in 2021, is delivered by UQ Health Care in partnership with Health and Wellbeing Queensland, along with key stakeholders: The University of Queensland, Griffith University, Metro South Hospital and Health Service, and Brisbane South Primary Health Network. The clinic provides a range of group and individual allied health services, including physiotherapy, exercise physiology, dietetics, social work, and health psychology. Students from across these disciplines, and others including public health and pharmacy, are integrated into the service delivery, supervised by interprofessional clinical educators.

### SSBC Australia Coaches

#### Overview

SSBC Australia coaches will be recruited at each of the sites using recruitment strategies identified in partnership with the delivery site. For The Y, it is expected that most coaches will be existing staff identified by the site leads as suitable for program delivery. For Logan Healthy Living, it is expected that most coaches will be drawn from students undertaking their placement at the site during the study period. Importantly, SSBC Australia coaches are not required to have any professional qualifications and can include lay volunteers and students. All coaches are required to be 18 years or older, meet the site-level requirements for volunteers at their respective sites, and pass the competency assessment for SSBC Australia intervention delivery. All coaches are also required to sign a nondisclosure agreement prior to undertaking the SSBC training as part of the Canadian-based requirements.

For Logan Healthy Living, all students, from any degree, undergoing at least a 5-week work integrated learning placement during the study period (and beyond depending on findings from the study) will be required to undertake the SSBC Australia training as part of their placement experience. Students can then opt in to provide data collected as part of this standard process to the research project and to deliver the SSBC Australia program to clients. Only those who provide consent for the research will be eligible to deliver the program to clients, providing they meet other eligibility requirements.

#### Target Sample Size—Coaches

There is no target sample size for coaches. Each Y site is required to have at least 2 trained coaches, while the Logan Healthy Living site is expected to have a small number of trained clinicians and a larger number of trained student coaches (anticipated total n≈50, mostly from Logan Healthy Living).

### Program Participants (Clients)

#### Overview

Program participants (clients) will be recruited at each of the sites using recruitment strategies identified in partnership with the delivery site. Recruitment strategies are expected to include but are not limited to listserv mailouts, on-site promotion, establishment of primary care and public health care referral pathways, promotion through local community groups, and health information showcases. Referral sources and referral strategies will be tracked by the project team.

The recruitment materials will direct potentially interested clients to complete an online expression of interest (EOI) and screening survey (REDCap). This survey, which was based on the Canadian SSBC eligibility survey, is anonymous until participants reach the consent stage, with the survey stopped if a participant does not meet the inclusion criteria at each of the staged steps. Ethics for this EOI and screening survey was obtained from The University of Queensland Low and Negligible Risk Human Research Ethics Committee (#2024/HE001280).

The EOI and screening survey will include the AUSDRISK as well as questions on glycosylated hemoglobin and fasting blood glucose level (if known). Permission to use the AUSDRISK, which is a simple yet valid and reliable risk assessment tool to predict incident type 2 diabetes within the next 5 years [36], was granted from the Australian Government Department of Health and Aged Care. It comprises a series of questions about diabetes risk factors including age, sex, personal and family history of high blood glucose, First Nations background (Aboriginal, Torres Strait Islander, Pacific Islander, and Māori), other ethnic minority background (Asian, Middle Eastern, North African, and Southern European background), if taking medication for hypertension, smoking status, diet, exercise habits, and waist measurement. A diabetes risk score between 0 and 38 will then be calculated, with scores being assigned according to risk for each factor, where a higher score indicates a higher risk of developing type 2 diabetes in the next 5 years.

#### Eligibility and Consent

Adults who are not pregnant (18 years or older) with a AUSDRISK score of 12 or over (considered high risk) or between 6 and 11 (considered intermediate risk) with at least 1 modifiable risk factor (smoking, low fruit and vegetables, low physical activity, and high waist circumference), or self-reported prediabetes or a glycosylated hemoglobin of 5.7% to 6.4% or fasting blood glucose of 5.6 to 6.9 mmol/L (if provided), able to provide informed consent, and able to attend at least 1 of the delivery sites, will be considered eligible and invited to complete the consent form. Information on comorbid conditions will also be captured at this point.

Participants who provide consent will then be automatically sent an information pack (via REDCap), tailored to their preferred site, which provides a guide to the SSBC Australia program and instructions for next steps. The site that the client indicates as their preferred site will also be notified of this potential client, along with information about their risk level. Participants will be encouraged to contact the site directly to support the enrollment process, depending on site preferences. Eligibility will be reconfirmed as part of this enrollment process. Once the client has been confirmed eligible by the site, they will be onboarded into the REDCap client database.

#### Target Sample Size—Participants

The target sample size is 500 participants enrolled (400 from the Y Queensland sites and 100 from the Logan Healthy Living site) for the 2-year researcher-led recruitment window, with no maximum sample size. This target sample size was determined based on the anticipated feasibility of recruitment. This sample size of 500 across 5 sites is sufficient to provide 80%-90% power with 5% 2-tailed significance to detect a 60 minute per week change in self-reported MVPA, which requires sample size of 394-528 based on assumptions of *r*=0.4, SD 330, 20% attrition, and intraclass correlation=0.001 (design effect=1+0.001(100–1)=1.099) informed by unpublished data from similar programs delivered in Logan and The Y sites.

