The Australian delivery of the SSBC program has been informed by a program of exploratory preimplementation work. This included a needs assessment within the community, preliminary discussions with the sites, and exploration of the appropriateness of the Canadian-developed SSBC coach training for the Australian context. The needs assessment was conducted via a cross-sectional survey with 575 community members of The Y (formerly known as The YMCA) across 20 Y Queensland sites [32]. Findings showed that there was both a need and a desire for a diabetes prevention program, with 46% of participants showing elevated risk of developing type 2 diabetes in the next 5 years according to the Australian Type 2 Diabetes Risk Assessment Tool (AUSDRISK) score [36], and 68% of participants expressing interest in taking part in such a program [32].

The preliminary site-level discussions involved interviews with site leads and other key staff members at each of the sites, with the Consolidated Framework for Implementation Research (CFIR) [37] used to guide the semistructured interview questions. An initial interview was conducted online, followed up with interviews on-site at each of the 5 sites. Findings highlighted that there was variation across sites in terms of the equipment available (both for assessment and exercise), services offered, staffing availability, and experience in implementing research projects and working with university partners. All sites catered to an aging population (appropriate for the SSBC intervention), were focused on serving the communities in which they worked, and had established communication channels available for program promotion. Findings confirmed that the sites identified for delivery were suitable, but site-specific protocols for implementation would be required.

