#### Data Analysis

Context, adoption, reach, implementation, and sustainability outcomes will be described. To evaluate client-level effectiveness and maintenance, changes from pre- to postintervention, as well as over the relevant maintenance time points, will be assessed using linear mixed models, correcting for repeated measures and cluster (site) using random intercepts, and adjusting for baseline values of the outcome. Analyses will be of evaluable cases, adjusting for predictors of missing data, with sensitivity analysis involving multiple imputation to test the robustness of conclusions to missing data handling choices. Effectiveness of the training will be assessed by describing competency attainment and testing changes from pre- to posttraining in confidence and knowledge scores, using 2-tailed paired *t* tests or nonparametric paired tests as appropriate. These tests ignore clustering due to the expected very small sample within each of the Y sites as well as the fact the training is provided centrally (unlike the intervention). Instead, exploratory analyses will test effectiveness in relevant subgroups (eg, Y coaches and student coaches from Logan Healthy Living).

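### The 80%-90% power at 500 enrolled rests on client-level degrees of freedom and a near-zero ICC not tied to change; with inference based on five sites it is about 67%-69%

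*Protocol article*

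**What the plan says.** Under Target Sample Size—Participants, the Protocol article sets a target of 500 enrolled, 400 from four Y Queensland sites and 100 from Logan Healthy Living. The number was chosen on recruitment feasibility. It then claims "80%-90% power with 5% 2-tailed significance to detect a 60 minute per week change in self-reported MVPA", "which requires sample size of 394-528", assuming a pre-post correlation of 0.4, an SD of 330, 20% attrition and "intraclass correlation=0.001 (design effect=1+0.001(100–1)=1.099) informed by unpublished data". It does not say whether the ICC describes MVPA level or change in MVPA.

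Under Data Analysis, pre-to-post change is to be assessed with linear mixed models "correcting for repeated measures and cluster (site) using random intercepts", also adjusting for the baseline value of the outcome. The section does not say whether preprogram values are outcome rows or only a covariate.

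The Introduction reports from the preimplementation interviews: "Findings highlighted that there was variation across sites in terms of the equipment available", and likewise in services, staffing and research experience. The section on individual coaching sessions allows sites to replace or supplement parts of the core program.

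**The concern.** Both the sample size and the analysis treat the five sites as random clusters. A design effect inflates the variance for clustering. It does not account for that between-site variance having to be estimated from five sites, which leaves 4 degrees of freedom. A power figure built on several hundred degrees of freedom is therefore more favourable than the analysis can deliver if its inference respects the clusters.

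Two further points are left open. For a pre-post contrast the relevant ICC is that of the change, and the article does not say that 0.001 is that quantity. And whether the site random intercept captures site differences in change depends on how the outcome is set up, which the article does not settle. The results are meant to inform expansion to other sites, so between-site uncertainty belongs in the intervals.

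**Working it through.** **Inputs** (Target Sample Size—Participants): SD 330, r = 0.4, change 60 min/week, two-sided alpha 0.05, attrition 20%, ICC 0.001, design effect 1.099, five sites.

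**1. Reproducing the plan's figure.**
- SD of change = 330 × √(2 × (1 − 0.4)) = 361.5.
- A paired t-test on change needs n = 287 for 80% power and n = 384 for 90%, using n − 1 degrees of freedom (286 and 383).
- Enrolled: 287 × 1.099 / 0.8 = 394.3 and 384 × 1.099 / 0.8 = 527.5, which match 394 and 528.
- A normal approximation gives 391 and 524, close but not exact. The number of sites enters only through the cluster size of 100.

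**2. Power at 500 enrolled (400 evaluable), ICC 0.001.**
- With the plan's design effect, SE = 361.5 × √(1.099/400) = 18.95. With 80 evaluable per site the design effect is 1 + 0.001 × 79 = 1.079 and SE = 18.78.
- Normal reference (critical value 1.96): 88.6% and 89.2%.
- Noncentral t on 5 − 1 = 4 df (critical value 2.776): 66.4% and 67.1%.
- 95% interval half-width with SE 18.95: 1.96 × 18.95 = 37.1 min/week, against 2.776 × 18.95 = 52.6.
- Simulation (five sites of 80, site random intercept on change): about 84% with a normal reference and about 69% with Satterthwaite-type df.

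**3. Sensitivity to the ICC of change.** Values above 0.001 are assumptions, not figures from the article. With 80 per site:

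| ICC of change | Design effect | Power, normal | Power, 4 df |
|---|---|---|---|
| 0.001 | 1.079 | 89% | 67% |
| 0.005 | 1.395 | 80% | 57% |
| 0.01 | 1.790 | 70% | 47% |
| 0.02 | 2.580 | 54% | 35% |

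For scale, the implied between-site SD of change is √0.001 × 361.5 ≈ 11 min/week at ICC 0.001 and √0.01 × 361.5 ≈ 36 at ICC 0.01.

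**4. What the site intercept does.**
- Form A: end-of-program value or change is the outcome and baseline is a covariate. A site random intercept then carries site differences in change.
- Form B: preprogram and end-of-program values are both outcome rows. The site intercept is common to both and cancels from the change, so a site-by-time effect is needed.

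Simulated two-sided type I error with five sites of 80:

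| ICC of change | Form A, normal reference | Form B, no site-by-time term |
|---|---|---|
| 0.001 | 4.3% | 5.9% |
| 0.01 | 7.8% | 14% |
| 0.02 | 9.8% | 22% |

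A t-test on the five site means (4 df) stayed near 5% throughout.

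**The case against.** The arithmetic is right on its own inputs, and clustering is addressed in both the sample size and the model. The ICC is said to come from similar programs at Logan and The Y, which are the same organisations. Four degrees of freedom is the conservative reference: if site variance in change is truly close to zero, the client-level figure is nearly right. Even a site random intercept on change with a normal reference gives about 84%, inside the stated range. The reported variation concerns equipment, services and staffing, not MVPA change, so it is no direct evidence against 0.001. An article may also leave the df method to a fuller document. Finally, 500 was set by feasibility, so power plays a supporting role.

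Most of this stands, and it limits the size of the point. It does not rescue the stated power as a description of inference from five clusters, because a small-sample df method, wherever it is specified, brings the figure to about 69%.

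A reader might go further and infer that the site random intercept misses site differences in change altogether, so that the primary test is seriously anti-conservative (14% to 22%). The article does not support that. It also adjusts for baseline, which fits Form A at least as naturally, and there the intercept does its job. The 14% and 22% need both Form B and ICCs ten to twenty times the stated value. At 0.001 the error rate is close to nominal under either form.

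**Conclusion.** The point holds for the power statement, and conditionally for the model. The claim that "This sample size of 500 across 5 sites is sufficient to provide 80%-90% power" depends on client-level degrees of freedom and on an ICC of 0.001 that is not tied to change. At that same ICC, inference that respects five sites has about 67% power on 4 df or 69% with Satterthwaite-type df, against 84% with a normal reference and 89% by the plan's formula. Lower figures rest on assumed ICCs of change up to 0.02.

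The random site intercept is adequate if end-of-program MVPA or change is the outcome with baseline as covariate. It is not adequate if preprogram values are also outcome rows. At ICC 0.001 this hardly affects type I error (4.3% or 5.9%). It matters from about 0.01 upward (7.8% or 14%), a value that the article neither gives nor rules out for change. The figures assume equal sites of 80 evaluable clients, except where the plan's own design effect of 1.099 is used.

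**What to change.** - **Model form.** State that end-of-program MVPA, or change, is the outcome, with baseline as covariate and a site random intercept. If preprogram values are kept as outcome rows, add a site-by-time random effect.
- **Inference.** Name a small-sample df method such as Satterthwaite or Kenward-Roger.
- **Sensitivity.** Report the five site-specific changes with a t interval on the site means (4 df).
- **Power statement.** Say that the ICC must be that of change in MVPA, and whether the unpublished 0.001 is. Give power at 500 enrolled on 4 df (about 67% at ICC 0.001) beside the large-sample figure, over an assumed ICC range of 0.001 to 0.02.

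The cost is a change of wording, wider intervals and a less favourable stated power. The recruitment target can stay as it is, since it was set by feasibility.
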